#### Sample Size

The sample size was calculated using the standard formula for comparing 2 independent means in a parallel-group design using several assumptions.

On the basis of previous studies in dialysis populations, an estimated SD of 5 g/L was used to account for heterogeneity and to avoid underestimation of sample size. Notably, studies by Kalantar-Zadeh et al [17] and Rambod et al [18] reported serum albumin SDs ranging from 1.9 to 4.4 g/L, while a study by Limwannata et al [19] reported an SD of 5.0 g/L.

A clinically meaningful difference (δ) of 3 g/L (0.3 g/dL) was selected as it is consistent with differences in serum albumin levels observed across dialysis populations in previous studies. For instance, variations of 0.3 to 0.4 g/dL are observed between cohorts reported in studies by Rambod et al [18] and Limwannata et al [19]. Additionally, serum albumin is a well-established predictor of morbidity and mortality in patients undergoing dialysis, and even modest changes are considered clinically relevant in reflecting improvements in nutritional status [17].

Using the formula mentioned below, a 2-sided significance level of.05 (Zα/2=1.96) and 80% power (Zβ=0.84) were used to calculate the sample size. As a result, a minimum of 44 participants per group was required. After accounting for an anticipated 10% dropout rate, the sample size was rounded up to 50 participants for each group, with a total sample size of 100 participants. As repeated measurements will be conducted at baseline, 3 months, and 6 months, the calculated sample size is considered conservative.

The sample size was calculated using the standard formula for comparing 2 independent means in a parallel-group design, as shown below:

[figure not shown]

Where n is the sample size per group, Zα*/*2 is the standard normal deviate for a 2-sided significance level (1.96 for *α*=.05), Zβ is the standard normal deviate for power (0.84 for 80% power), σ is the SD, and δ is the expected difference between groups.

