**Inclusion criteria**
Adult outpatients (aged >18 years) attending peritoneal dialysis (PD) clinic visitsHave undergone peritoneal dialysis for at least 6 monthsHave a serum albumin level <40 g/LHave a malnutrition inflammation score of mild, moderate, or severeAgreed to follow the dietary instructions based on the randomization assignmentAgreed to attend baseline visits and additional follow-up appointments at months 1, 3, and 6 postrandomization, either in person or via telehealth, and respond to monthly or more frequent phone calls

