### Statistical Analysis

Statistical methods are detailed in Table 4. Data will be analyzed using SPSS (version 28; IBM Corp). Normality of continuous data will be tested using the Kolmogorov-Smirnov test.

**Table 4 table4:** Summary of the statistical analysis.

Study outcomes	Variables	Statistical analysis
Primary or main outcome	Serum albumin	GLM^a^-repeated measures (time×group interaction)
Secondary outcomes	Anthropometric data Biochemical data Dietary adequacy Physical function Quality of life Appetite and food satisfaction Dialysis adequacy	GLM-repeated measures (time×group interaction)
Exploratory or feasibility outcomes	Dietary adherence or compliance Retention rate	Descriptive statistics and chi-square test

^a^GLM: generalized linear model.

The primary analysis will evaluate changes in serum albumin from baseline to 3 and 6 months between intervention and control groups. A generalized linear model for repeated measures will be used to assess time, group, and interaction effects. Analyses will follow the intention-to-treat principle, with missing data handled using the last observation carried forward method. Adjustment for potential confounders such as age, sex, dialysis duration, and baseline nutritional status will be performed using multivariable models. Bonferroni correction will be applied for multiple comparisons. Secondary outcomes, including anthropometric, biochemical, dietary, MIS, physical function, QOL, appetite, and dialysis adequacy parameters, will be analyzed using similar repeated-measures approaches. Statistical significance will be set at *P*<.05.

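### Last observation carried forward as the only missing-data rule for albumin biases the 6-month difference and usually understates its uncertainty

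*Protocol article*

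**What the plan says.** All of this is in the protocol article. The Statistical Analysis section states the primary contrast: "The primary analysis will evaluate changes in serum albumin from baseline to 3 and 6 months between intervention and control groups". The model is given as "A generalized linear model for repeated measures will be used to assess time, group, and interaction effects". On the analysis set and missing values it says "Analyses will follow the intention-to-treat principle", "with missing data handled using the last observation carried forward method". No other missing-data method is named. Secondary outcomes are to be analysed by similar repeated-measures methods, so the rule reads as covering them too.

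Three other places decide what the rule does in practice:

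- **Research Flow and Table 1:** outcomes are assessed at baseline, month 3 and month 6 only.
- **Participant Withdrawal and Dropouts:** participants may be withdrawn for missing at least half of the visits, for compliance below 50% at three consecutive monthly reviews, or for a clinical condition that needs intervention or could affect the outcomes. Data gathered before withdrawal are kept. Nothing is said about collecting albumin afterwards.
- **Sample Size:** dropout is expected to be 10%, not split by arm or by time.

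**The concern.** Carrying a value forward assumes that albumin stays where it was last seen. The trial asks whether albumin changes over 6 months, in patients enrolled because it is low. A participant with no albumin after baseline is scored as having changed by exactly zero. One lost after month 3 is scored as having had no further change.

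The withdrawal criteria make it unlikely that those lost resemble those who stay. The protein-source item of the compliance score differs by arm (Table 2), so unequal withdrawal is plausible. The filled-in values then enter the repeated-measures model as if they had been measured. At stake are the size of the primary estimate, the honesty of its interval and, if dropout is unequal, the arm that the error favours.

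**Working it through.** **Inputs from the Sample Size section.** "a 2-sided significance level of.05 (Zα/2=1.96) and 80% power (Zβ=0.84) were used to calculate the sample size"; "an estimated SD of 5 g/L was used to account for heterogeneity"; "A clinically meaningful difference (δ) of 3 g/L (0.3 g/dL) was selected"; dropout 10%; 50 per arm.

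**Assumptions not in the article.** The SD of change is 5 g/L, which follows from a visit SD of 5 and a correlation of 0.5: √(2 × 25 × (1 − 0.5)) = 5. Dropout timing, its split by arm and any common drift are also assumed. A rate of 20% is included to show how the problem grows.

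**1. The plan's own figure.** n = 2 × (5 × (1.96 + 0.84)/3)² = 43.56, so 44 per arm. 44/0.9 = 48.9, so 49, rounded to 50. The stated figure reproduces.

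**2. Dilution with equal dropout d and a true effect of 3 g/L.**
- Baseline carried: 3(1 − d), which is 2.7 at 10% and 2.4 at 20%.
- Month 3 carried with half the effect present: 3(1 − d) + 1.5d, which is 2.85 at 10% and 2.7 at 20%.

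**3. Standard error with baseline carried.** The variance of the filled-in change is 25(1 − d) + 9d(1 − d) in the intervention arm and 25(1 − d) in the control arm.
- d = 0.1: √((23.31 + 22.50)/50) = 0.957. Observed data give 5√(2/45) = 1.054. The shortfall is about 9%. The value is also below the 5√(2/50) = 1.000 that complete data would give.
- d = 0.2: √((21.44 + 20.00)/50) = 0.910, against 5√(2/40) = 1.118. The shortfall is about 19%.

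**4. Coverage of the true 3 g/L by the 95% interval.** Φ(b + 1.96) − Φ(b − 1.96), where b is bias/SE.
- d = 0.1: b = 0.3/0.957 = 0.313, coverage 93.9%.
- d = 0.2: b = 0.6/0.910 = 0.659, coverage 89.9%.

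**5. Unequal dropout with no true effect.** Take 20% dropout in the intervention arm and 5% in control, a common change of −2 g/L, and baseline carried. The filled-in mean changes are 0.80 × (−2) = −1.6 and 0.95 × (−2) = −1.9, a spurious +0.3 g/L for the intervention. With a common change of +2 g/L it is −0.3 g/L.

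**6. Simulation check.** 2,000 trials per setting, 50 per arm, month-6 albumin adjusted for baseline, correlation 0.5, half the dropouts before month 3 and half after, dropout at random.

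| Setting | LOCF estimate (g/L) | LOCF SE | Observed-case SE | LOCF coverage |
|---|---|---|---|---|
| Effect 3, 10% dropout | 2.76 | 0.856 | 0.913 | 92.8% |
| Effect 3, 20% dropout | 2.57 | 0.846 | 0.971 | 91.5% |

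The SE shortfalls are 1 − 0.856/0.913 = 6% and 1 − 0.846/0.971 = 13%. With no effect and 20% against 5% dropout, drifts of −2 and +2 g/L gave spurious differences of about +0.2 and −0.2 g/L. With no effect, no drift and equal dropout there was no bias, and the test rejected 4.5–5.0% of the time (correlations 0.5 and 0.7).

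**The case against.** **Size.** The strongest reply is that the harm is modest at the planned dropout: 0.15–0.3 g/L on 3 g/L. Withdrawal for compliance needs three failed monthly reviews in a row, so those participants may well have a month-3 albumin, which points to the smaller figure. Power hardly moves: in the closed form at 10% dropout it is 80.5% with carried values against 81.2% with observed data. This stands. The damage is to the estimate and its interval more than to the test.

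**The standard error claim.** A reader might infer that carried values always make the standard error too small and inflate false positives. The calculations do not support that. The model standard error roughly matches the spread of the carried-forward estimator itself, so the under-coverage comes mainly from bias. In a simulation at 10% per arm with dropout driven by low month-3 albumin, the standard errors were almost equal (0.832 against 0.838). In another with dropout of that kind (no effect, −2 g/L drift, 20% against 5%), carrying forward happened to give a difference near zero, while month-6 observed cases alone gave 0.21 g/L. So analysing only month-6 completers is no remedy. The replacement must also use the month-3 values.

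**Telehealth.** The inclusion criteria allow follow-up "either in person or via telehealth", and a reader might infer that this makes albumin missing. It does not follow. The Biochemical Data section takes laboratory values from hospital records, and the study runs alongside routine clinic visits.

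**Death, transplant or transfer to haemodialysis.** A reader might also infer that values would be carried past these events. The article does not discuss them, and their handling may sit in a fuller document.

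**Conclusion.** The point holds in a limited form. The article fixes carrying forward as the only missing-data rule for the primary analysis, and nothing elsewhere in it softens that.

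Given a true 3 g/L effect and equal dropout, the expected estimate is about 2.7–2.85 g/L at 10%, with coverage near 94% when baseline is carried. It is 2.4 g/L with coverage near 90% at 20% and baseline carried. With unequal dropout and drift the direction cannot be known in advance; the size is about 0.3 g/L for 20% against 5% and a 2 g/L drift. The standard error is usually, not always, below what the observed data support, by about 6–9% at 10% dropout. Type I error is not raised when there is no effect, no drift and equal dropout.

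All of these sizes rest on SD 5 g/L, a correlation of about 0.5 and the dropout patterns stated. They grow if dropout exceeds the planned rate.

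**What to change.** - Delete last observation carried forward. Fit a likelihood-based linear mixed model (SPSS MIXED) to all observed month-3 and month-6 albumin values, with arm, visit, arm × visit, baseline albumin, baseline × visit and an unstructured covariance. The month-6 arm contrast answers the primary objective.
- Extract month-3 and month-6 albumin from hospital records for withdrawn participants who consent. This matters most for those lost before month 3, who otherwise add no follow-up value to the model.
- Add a delta-adjusted sensitivity analysis for values missing not at random, with the shift varied separately by arm. It belongs with the new primary method; its absence from the article is not itself a fault.
- Use the same model in place of carrying forward for the continuous secondary outcomes.

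The cost is a change of analysis procedure within the software already named, plus some record extraction. No larger sample is needed: 50 × 0.9 = 45 completers per arm give about 81% power for 3 g/L. With 9 participants recruited at submission, the change can be made well before outcome data are analysed.

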**Objective:**

This study aims to determine the effectiveness of a plant-focused dietary intervention compared with a standard-of-care renal diet on nutritional status, measured by changes in serum albumin, among malnourished patients undergoing PD over 6 months.

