#### Research Flow

This study protocol is adapted from a similar ongoing clinical trial involving patients with CKD with diabetes mellitus in the United States [16]. Figure 1 shows a diagram outlining the research flow. The study begins with participant screening, recruitment, and baseline assessment conducted on the same day. Following baseline assessment, participants are then randomized into either the intervention group receiving a plant-focused dietary intervention or the control group receiving a standard renal dietary intervention.

A 2-week familiarization phase is implemented immediately after randomization as part of the intervention period. During this phase, participants begin following their assigned dietary intervention and receive additional guidance and closer monitoring to support early adaptation and adherence. This phase is intended to facilitate understanding of the dietary protocol and to identify and address potential challenges early, rather than to assess eligibility or introduce selection bias.

Participants from both groups are instructed to continue the assigned dietary intervention for 6 months. Key outcome assessments are conducted at baseline (0 months), midpoint (3 months), and end line (6 months). Data collected will be analyzed for subsequent report writing and publication.

The intervention and study procedures, including screening, recruitment, data collection, and intervention delivery, will be conducted by a registered dietitian. Health care staff at the study site will assist with clinical procedures such as blood collection.

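### Month 0 is modelled as a response; adjustment for an outcome's own baseline is not named for the non-nutritional secondary outcomes and is undefined for albumin, which can cost precision

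*Protocol article*

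**What the plan says.** All references are to the Protocol article.

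- **Model.** Table 4 (Statistical Analysis) gives the secondary outcomes "GLM-repeated measures (time×group interaction") and has the same entry for albumin. The text adds: "A generalized linear model for repeated measures will be used to assess time, group, and interaction effects".
- **Contrast.** "The primary analysis will evaluate changes in serum albumin from baseline to 3 and 6 months between intervention and control groups".
- **Place of month 0.** Research Flow: "Key outcome assessments are conducted at baseline (0 months), midpoint (3 months), and end line (6 months"). Sample Size also counts baseline as one of the repeated measurements: "As repeated measurements will be conducted at baseline, 3 months, and 6 months, the calculated sample size is considered conservative".
- **Covariates.** "Adjustment for potential confounders such as age, sex, dialysis duration, and baseline nutritional status will be performed using multivariable models". The list is introduced as examples. The secondary outcomes are to be handled by similar repeated-measures methods, with no further covariate named.
- **Meaning of nutritional status.** The Objective in the abstract ties it to albumin: "standard-of-care renal diet on nutritional status, measured by changes in serum albumin, among malnourished patients undergoing PD over 6 months". The Malnutrition Inflammation Score section assesses nutritional and inflammatory status by MIS. In Research Objectives, the second secondary objective uses baseline nutritional status for a wider set that includes knowledge, attitude and practices.

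**The concern.** With month 0 as a level of the time factor, the time×group contrast at month 6 is the difference between arms in change from month 0. That contrast subtracts the whole baseline value. When the correlation between baseline and follow-up is below 1, this removes too much. The unneeded part adds noise, and the estimate depends on any chance difference between arms at baseline. Entering the outcome's own baseline as a covariate avoids both.

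For outcomes that are not themselves nutritional status, the only baseline measure among the named covariates is a different variable. For albumin, whether the primary model is baseline-adjusted depends on how an undefined term is later read. At stake are the width of the confidence intervals and the power, using a measurement the trial already takes. The statement that the sample size is conservative is also affected.

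**Working it through.** **Inputs.** From Sample Size: SD 5 g/L, difference 3 g/L, two-sided α 0.05 (1.96), power 80% (0.84), 44 per group before dropout, 50 after. The SD is taken as that of albumin at one time point, as the cited albumin SDs suggest. Assumed: equal SD at months 0 and 6, and a correlation ρ between them. The article gives no ρ, so a range is shown.

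**The plan's own figure.** n = 2 × (1.96 + 0.84)² × 5² / 3² = 2 × 7.84 × 25 / 9 = 43.56, so 44 per group. With 10% dropout, 44 / 0.9 = 48.9, so 49, which the plan rounds up to 50. The stated figures reproduce.

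**Two versions of the month-6 contrast.**

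- Change score: SD = 5 × √(2(1−ρ))
- Own baseline as covariate: SD = 5 × √(1−ρ²)
- Ratio of variances, adjusted over change: (1−ρ²) / (2(1−ρ)) = (1+ρ)/2
- SE = SD × √(2/44); power = Φ(3/SE − 1.96)

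| ρ (assumed) | SD, change / adjusted | SE, change / adjusted (g/L) | Power at 44 per arm | n per arm for 80% | Variance ratio |
|---|---|---|---|---|---|
| 0.3 | 5.92 / 4.77 | 1.26 / 1.02 | 66% / 84% | 62 / 40 | 0.65 |
| 0.4 | 5.48 / 4.58 | 1.17 / 0.98 | 73% / 87% | 53 / 37 | 0.70 |
| 0.5 | 5.00 / 4.33 | 1.07 / 0.92 | 80% / 90% | 44 / 33 | 0.75 |
| 0.7 | 3.87 / 3.57 | 0.83 / 0.76 | 95% / 98% | 27 / 23 | 0.85 |
| 0.8 | 3.16 / 3.00 | 0.67 / 0.64 | 99.4% / 99.7% | 18 / 16 | 0.90 |

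The confidence interval narrows by 1 − √((1+ρ)/2): 19%, 13%, 8% and 5% at ρ 0.3, 0.5, 0.7 and 0.8.

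**The overall interaction test.** Simulating the 2-df time×group test (4,000 runs, 45 per arm, compound symmetry, a 3 g/L effect at both visits) gives power without and with own-baseline adjustment of 69% and 92% at ρ 0.3, 84% and 95% at 0.5, and 97% and 99% at 0.7.

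**The claim that the size is conservative.** The change contrast needs no more than 44 per arm only if 2(1−ρ) ≤ 1, that is ρ ≥ 0.5. At ρ 0.4 and 0.3 it needs 53 and 62, above even the 50 to be randomised. With own-baseline adjustment 44 is enough at every ρ, because 1−ρ² never exceeds 1.

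**Chance imbalance.** At 50 per arm the SE of the baseline albumin difference is 5 × √(2/50) = 1.0 g/L. Each 1 g/L of imbalance moves the change-score estimate by −(1−ρ): 0.3 g/L in size at ρ 0.7 and 0.5 g/L at ρ 0.5. Simulated slopes were −0.68, −0.50 and −0.30 at ρ 0.3, 0.5 and 0.7, and about 0 after adjustment.

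**If the albumin covariate is baseline albumin.** Entered with a covariate-by-time term, it makes the change contrast the same as an analysis of covariance. On one simulated data set (44 per arm, ρ 0.5) both gave an estimate of 2.897 and SE 0.858. On that reading nothing is lost for albumin.

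**The case against.** The strongest objection concerns the primary outcome. The article measures nutritional status by albumin in its stated objective, so baseline nutritional status can naturally be read as baseline albumin. The covariate list is also open, and a condensed article may leave the list for each outcome to an analysis plan. This stands to the extent that omission of baseline albumin is not shown. The albumin figures above are therefore conditional on the other reading. It does not dispose of the point: the article uses the term in more than one sense, and for quality of life, appetite, physical function, lipids, hs-CRP or Kt/V it is not the outcome's own baseline on any ordinary reading.

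A second objection is that a change-from-baseline analysis is legitimate and matches the primary objective as worded. That stands too. A reader might infer that chance baseline imbalance biases the trial. It does not on average under randomisation: the shift is regression to the mean, conditional on the imbalance seen, and the change-score SE already includes that variability.

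A reader might also infer that using albumin as both response and covariate is invalid. Simulated type I error was 5.0–5.4% for the F tests. It reached 7% only for a pooled-error month-6 contrast, which the article does not specify.

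Finally, the loss is small if ρ is high. That is correct, but the article gives no ρ on which to rely.

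**Conclusion.** The point holds as one of efficiency and definition, not of validity. Month 0 is a response level for albumin and the secondary outcomes. Own-baseline adjustment is not named for the secondary outcomes outside nutritional status, and is undetermined for albumin. Where it is absent, the variance is larger by the factor 2/(1+ρ): 1.54 at ρ 0.3, 1.33 at 0.5 and 1.18 at 0.7, assuming equal variances at the two visits. For albumin this applies only if the named covariate is MIS or another index, or if baseline albumin is entered without a covariate-by-time term.

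The documents do not support saying that the trial is underpowered. At ρ of 0.5 or more, the change contrast reaches 80% power with 44 per arm. They support only that the size is not assured to be conservative, since that fails below ρ 0.5.

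**What to change.** For albumin and every continuous secondary outcome, take months 3 and 6 as the responses. Include visit, arm, arm×visit, that outcome's own month-0 value and its interaction with visit. An equivalent constrained-baseline model would serve as well. Keep age, sex and dialysis duration as covariates. State which variable baseline nutritional status denotes and, if it is MIS, that it is in addition to the outcome's own baseline. Either drop the remark that repeated measurement makes the sample size conservative, or tie it to the baseline-adjusted analysis.

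The cost is a change of analysis wording. No new data or visits are needed, and the effect is then reported as a baseline-adjusted difference between arms at months 3 and 6. The Study Timeline section reports 9 participants recruited at submission, so the change can be made early in the trial.

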### Trial Registration

This study has been registered with ClinicalTrials.gov (NCT07157397) and National Medical Research Register (NMRR ID-26-00114-LAK).

### Ethical Considerations

#### Ethics Approval

This study has obtained ethics approval from the Universiti Kebangsaan Malaysia Research Ethics Committee (JEPUKM; JEP-2025-812). The study will be conducted in accordance with the Declaration of Helsinki, Malaysian Good Clinical Practice Guidelines, and institutional policies. Any protocol deviations will be reported to the ethics committee as required. Adverse events will be monitored throughout the study period and followed up as appropriate. Participants will continue to receive standard clinical care throughout the trial.

A data monitoring committee is not required for this study due to the low-risk nature of the intervention. No interim analyses or stopping guidelines are planned due to the nature and duration of the study. Trial conduct will be monitored by the research team to ensure adherence to the study protocol. No formal external monitoring is planned due to the low-risk nature of the study.

